**Figure 1 F1:**
[figure not shown]
Flowchart of participant’s recruitment and trial design.

### Description of the intervention

#### Intervention group

The intervention will be done according to the patient’s willingness to reduce sitting time (stage of change), and considering whether the subject prefers a more or less intensive intervention: (a) precontemplative (not thinking about change) and contemplative (thinking about change), (b) ready to change with minimum professional support, or (c) ready to change with intensive professional support. All of them will be handed a card with the planned sessions and Mediterranean diet recommendations.

Precontemplative and contemplative patients (a) will be informed of the risks of being 6 or more hours sitting and will be asked about the importance and confidence for change. Ready to change patients (b and c) will be proposed an intervention based on 2–5 meetings (visits face-to-face or phone calls depending on the situation of each professional and patient) with a trained professional during 6 months. On those meetings, the professional will work on finding alternatives to progressively reduce SB by developing the same activities walking.

### Control group

Subjects assigned to the control group will be given information on the study and will be asked to continue their routine daily activities. They will receive their usual care from their primary care practice. Furthermore, the health professional will give the patient pamphlet with the Mediterranean diet recommendations. They will be followed at the end of intervention and at three, six and twelve months follow-up. At the following visits several parameters will be evaluated (see Outcome measures).

### Blinding – single blind

Baseline measures will be taken prior to allocation of randomisation. Independent investigators assessing participants at the end of the intervention and at three, six and 12 month follow-up visits or phone calls will be blind to the allocation of the treatment group. Participants will be asked not to discuss group allocation with the assessing professional. Moreover, the person who carries out the analysis of the data will not be involved in the investigation.

### Outcome measures

#### Main objective

The primary outcome is sitting time measured by using the activPAL device (PAL technologies, UK). It also will be measured with the Marshall questionnaire [19]. The study measure will be assessed at baseline, at the end of the intervention, and at three, six and twelve months follow-up.

Sitting time will be evaluated, moving from ≥6 hours daily sitting to less sitting time, and increasing the weekly number of METs. The activPAL enables to evaluate caloric expenditure, time sitting/lying, number of steps, standing time, walking time and the transitions from one position to another. This instrument has shown good validity and reliability in general population in a previous study [20]. Marshall questionnaire enables sitting time to be evaluated as a continuous variable by calculating the weekly minutes sitting, and classifying the subjects according to whether they are more or less hours sitting. This instrument has shown good validity and reliability in general population in a previous study [19].

#### Other specific objectives

Secondary outcomes for IG and CG include: (a) decreasing sitting time in work place in individuals involved in the intervention, measured with Occupational Sitting and Physical Activity Questionnaire (OSPAQ) [21]; (b) description of the development of health-related quality of life measured with EQ-5D (Euroqool Group: http://www.euroqol.org) (first and last session of the intervention, with follow up at three, six and twelve months after the intervention); (c) evaluation the evolution of the attitude towards the change in behaviours in relation to reduce sitting time using the Prochaska scale (Prochaska and DiClemente’s Stages of Change Model) [22]; (d) evaluation of physical inactivity, assessed with catalan version of Brief Physical Activity Assessment Tool (CBPAAT). The CBAFC enables physical inactivity as a categoric outcome and classifies subjects as ‘active enough’ or ‘insufficiently active’. This instrument showed good validity and reliability in general population in a previous study [23]; (e) evaluation of the number of daily steps walked, measured with DigiWalker 200w pedometer and activPAL posture monitor. Reliability and validity of these devices were previously assessed [20,24]; (f) evolution of anthropometric variables: BMI, triceps skinfold and waist circumference; and (g) description of the evolution of triglycerides, total cholesterol, HDL, LDL, glycemia and, glycated haemoglobin in diabetic patients (first and last session and 6 and 12 months after the intervention).

All parameters (not (g) outcome) will be assessed pre and post intervention in both groups and there will be a follow up in a face to face interview three, six and twelve months after the intervention.

Sociodemographic and health data will be also collected (age, marital status, educational level, blood pressure, BMI and associated pathologies).

### Data management and quality assurance

Data will be entered directly into an online questionnaire (SurveyMonkey: https://es.surveymonkey.com) by investigators at the time of the interview and baseline testing. Daily backups will be performed and transferred to the master database at least once a week. Random checks of data entry will be performed regularly and corrections made will be possible by checking against electronic records and by phoning professionals for patient’s information confirmation by independent investigators.

### Sample size

Since no previous intervention studies on caloric spend had been undertaken –similar studies report sedestation time- we consider that the current intervention is analogous to others proposed in other lifestyles such as tobacco consumption. Accepting an alpha risk of 0.05 and a beta risk < 0.10 in a bilateral contrast, 232 individuals are needed: 116 individuals in the IG and 116 in the CG in order to detect a difference ≥ 0.15 between the two. A proportion of 0.5 in one of the groups is to be assumed. A dropout rate of 20% is estimated. The sample size calculations were performed with the Granmo program (version 7.1).

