To effectively manage the increasing number of patients with obesity-related chronic illnesses, the medical community should embrace a major role in encouraging patients to make healthy lifestyle choices. Primary care is well suited to fill this need, because most of the population identifies a primary care clinician as their usual source of care [15].

There are few randomized controlled trials that assess the impact of interventions on the reduction in daily sitting time. Additionally, these studies have included small samples. A recent intervention with 92 subjects with type-2 diabetes achieved a reduction in daily sitting time of 23 min/day [16]. Another study with 12 patients with overweight and obesity showed an increase in walking time per day (146 to 203 min/day), increase in number of steps/day (4351 to 7080 steps/day) and decrease in sitting time (1238 to 1150 min/day) [17]. To our knowledge, there is no evidence on the effectiveness of an intervention based on reducing daily sitting time in adults with overweight and mild obesity and its sustainability in the long term.

The aim of the present study is to assess whether a sustained reduction of sedentary time is possible, and if so, to evaluate the effectiveness of an education-based intervention among overweight and mild obese adults attended in Primary Care in terms of reduction of sitting time. Secondary aims are to determine health benefits of the intervention among studied population.

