### Statistical methods

Analysis of effectiveness will be made followed by the intention to treat analysis. Descriptive statistics will be computed as customary [25,26]. Control and intervention groups will be checked for health and outcome measures and a baseline comparability analysis of the CG and IG in relation to the variables studied, will be carried out. An t-Student test or ANOVA will be used in the comparison of means if the variables follow a normal distribution and the U of Mann Whitney if they do not. For the other dimensions of the analysis, a covariance analysis (ANCOVA) for repeated measures will be carried out.

Multi-variate analysis will evaluate the change in the time of the described dependent variables, and comparisons between the CG and IG will be established. To do this multilevel linear models will be adjusted, one for each dependent variable. In the first level the individual path or the evolution of each individual over a long period of time (pre-post intervention, 3, 6 and 12 month follow- up) will be modelled. In the second level it will be adjusted according to the variables that refer to the individual; the intervention variable will be added (intervention or control) to the independent variables described earlier.

The level of statistical significance will be set at 0.05, and all tests will be two-tailed. Statistical analyses will be conducted using SPSS, version 17.0 (SPSS Inc, Chicago, IL).

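### The stated 90% power belongs to an unnamed proportion rather than to the planned comparison of activPAL sitting time, and 116 per arm does not give that power for the proportion either

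*Protocol article*

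**What the plan says.** Under Main objective the protocol article states: "The primary outcome is sitting time measured by using the activPAL device". Sitting time is also to be measured with the Marshall questionnaire. The same section describes the aim as participants moving from six or more hours of sitting a day to less, and notes that the Marshall questionnaire can also classify people by hours sitting.

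The Sample size section starts elsewhere. It opens "Since no previous intervention studies on caloric spend had been undertaken", adds that similar studies report sitting time, and continues "we consider that the current intervention is analogous to others proposed in other lifestyles such as tobacco consumption". It then gives the calculation: "Accepting an alpha risk of 0.05 and a beta risk < 0.10 in a bilateral contrast, 232 individuals are needed", made up of "116 individuals in the IG and 116 in the CG in order to detect a difference ≥ 0.15 between the two". One group is assumed to have a proportion of 0.5, and dropout is put at 20%. The event behind the proportion is not named.

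Statistical methods compares means by t-test or ANOVA (Mann-Whitney if not normal), adds repeated-measures ANCOVA, and for change over time says "To do this multilevel linear models will be adjusted, one for each dependent variable". It names no test of a proportion.

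The Background quotes two earlier results on sitting time. One is "A recent intervention with 92 subjects with type-2 diabetes achieved a reduction in daily sitting time of 23 min/day". The other is a fall from 1238 to 1150 min/day in 12 overweight and obese patients. The calculation uses neither.

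**The concern.** A sample size is a statement about one comparison: this outcome, this test, this difference. Here the calculation concerns a yes/no event, while the primary outcome is a duration and the planned analyses are of means. The reason given for borrowing from tobacco interventions is a lack of studies on caloric spend, yet the outcome to be powered is sitting time, for which the same sentence concedes that studies exist.

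The consequence lies in how the result can be read. With no target difference in minutes and no SD, a null result cannot be told apart from low power, and a positive result has no planning benchmark. The 90% figure would probably be quoted as the power of the primary comparison, which it is not.

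**Working it through.** **Inputs from the Sample size section:** two-sided alpha 0.05 (z = 1.960), power 0.90 (z = 1.282), proportions 0.50 and 0.65 (0.35 gives the same result), 116 per arm, dropout 20%.

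**1. The plan's own figure.** For two proportions with pooled variance under the null and p̄ = 0.575:

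n per arm = [1.960 × √(2 × 0.575 × 0.425) + 1.282 × √(0.50 × 0.50 + 0.65 × 0.35)]² / 0.15²

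= (1.3702 + 0.8856)² / 0.0225 = 226.2, so 227 per arm, or 454 in total.

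Allowing for dropout: 226.2 / 0.80 = 282.7 (283), or 227 / 0.80 = 283.75 (284) if rounded up first. The plan has 116 per arm. The unpooled formula gives 223 and the arcsine formula 227. Even at 80% power the requirement is 170 before dropout. None of these gives 116.

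**2. Power of 116 per arm for 0.50 against 0.65.** Power = Φ[(0.15√n − 1.3702) / √0.4775], with √0.4775 = 0.6910.

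- n = 116: (1.6155 − 1.3702) / 0.6910 = 0.355, power 64%.
- n = 93 (116 × 0.80 = 92.8): (1.4465 − 1.3702) / 0.6910 = 0.110, power 54%.

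**3. What the same number can detect on a mean.** For a two-sample t-test at one time point without baseline adjustment, the normal approximation is (z_α + z_β) × √(2/n). With n = 93 at 90% power this is (1.960 + 1.282) × √(2/93) = 0.475 SD. The exact t calculation gives 0.478 SD at 90% and 0.413 SD at 80%. With all 116 per arm the 90% value is about 0.43 SD.

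**4. In minutes.** The article gives no SD, so 60, 90 and 120 min/day are assumptions, as is the baseline correlation r = 0.5 in the column where the SD is multiplied by √(1 − 0.25). All rows use 93 per arm and two-sided 0.05. The 88 min/day is 1238 − 1150.

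| Assumed SD (min/day) | Detectable at 90%, unadjusted | Power for 23 min/day, unadjusted | Power for 23 min/day, r = 0.5 | Power for 88 min/day, unadjusted |
|---|---|---|---|---|
| 60 | 29 min/day | 74% | 85% | above 99% |
| 90 | 43 min/day | 41% | 52% | above 99% |
| 120 | 57 min/day | 26% | 32% | above 99% |

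The 88 min/day comes from 12 patients and is not presented as a difference between groups. The Background does not identify the 23 min/day as a between-group difference either.

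**The case against.** The best defence is that the proportion is a threshold form of the primary outcome. Everyone enters sitting at least six hours a day, Main objective speaks of moving below that, and the Marshall questionnaire can classify participants, so the share falling below six hours is an obvious candidate event. Under a normal model, 0.50 against 0.65 on such a threshold corresponds to a shift of about 0.385 SD, for which a t-test has about 74% power with 93 per arm and 83% with 116. This much stands: the planning target could be translated to the continuous scale if that were the event. But no responder endpoint is defined, the classification sentence concerns the questionnaire and not the activPAL, and no test of a proportion is planned. Even on this reading, power stays below 90%.

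Caloric spend is also not a stray reference. The description of Phase 2 names raising it as an aim, and Main objective mentions METs. It is still not the primary outcome.

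A reader might infer that the sample size says nothing about the primary comparison. That goes too far: any number per arm implies a detectable difference in SD units, as shown above. A reader might also infer that the trial is underpowered for sitting time. The article does not support that: the answer depends on an SD it does not give, one of its two cited changes would be detected almost surely, and baseline adjustment or the repeated follow-ups could improve precision.

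Finally, one may guess where 116 came from. A 0.20 difference at 80% power gives 93 per arm, or 117 with dropout, and 232 lies near the per-arm figure of 227. Neither matches the stated inputs, so both remain guesses.

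**Conclusion.** The point holds in two parts.

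First, the stated power is not the power of the planned primary comparison. The calculation, the primary outcome and the analysis are all in the article and do not match, so this is not a detail left to a fuller document.

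Second, the power claim fails on its own terms. The stated inputs need about 227 per arm before dropout and 283 to 284 after, and 116 per arm gives about 64% power, or 54% after 20% loss. This part needs no outside assumption.

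For mean sitting time, the planned number can detect about 0.48 SD at 90% power or 0.41 SD at 80%, unadjusted, with 93 evaluable per arm. Everything expressed in minutes rests on the assumed SDs. Whether 232 is enough for sitting time is therefore open. This should be corrected before the trial's power is relied on.

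**What to change.** Rewrite the Sample size paragraph for the difference between groups in mean activPAL sitting time (min/day), adjusted for baseline. Several post-baseline assessments are listed and none is named as primary in the article, so name the primary time point first. Give the target difference, the assumed SD and the baseline correlation, each with its source, and drop the tobacco analogy as the basis.

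Then state what the planned 232 can detect: about 0.48 SD at 90% power or 0.41 SD at 80% with 93 evaluable per arm, unadjusted, together with the value in minutes under the chosen SD. Withdraw the 90% power claim for the 0.15 difference, and say openly that 232 does not follow from those inputs.

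If a binary endpoint was intended, define the event, the instrument and the time point, plan an analysis of proportions for it, and correct the stated power.

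Cost: one rewritten paragraph. Restating what 232 can detect needs no extra patients. The downside is that the stated power becomes less favourable.

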**Method/Design:**

The study is a randomized controlled trial (RCT). Professionals from thirteen primary health care centers (PHC) will randomly invite to participate mild obese or overweight patients of both gender, aged between 25 and 65 years old, who spend 6 hours at least daily sitting. A total of 232 subjects will be randomly allocated to an intervention (IG) and control group (CG) (116 individuals each group). In addition, 50 subjects with fibromyalgia will be included.

Primary outcome is: (1) sitting time using the activPAL device and the Marshall questionnaire. The following parameters will be also assessed: (2) sitting time in work place (Occupational Sitting and Physical Activity Questionnaire), (3) health-related quality of life (EQ-5D), (4) evolution of stage of change (Prochaska and DiClemente's Stages of Change Model), (5) physical inactivity (catalan version of Brief Physical Activity Assessment Tool), (6) number of steps walked (pedometer and activPAL), (7) control based on analysis (triglycerides, total cholesterol, HDL, LDL, glycemia and, glycated haemoglobin in diabetic patients) and (8) blood pressure and anthropometric variables. All parameters will be assessed pre and post intervention and there will be a follow up three, six and twelve months after the intervention. A descriptive analysis of all variables and a multivariate analysis to assess differences among groups will be undertaken. Multivariate analysis will be carried out to assess time changes of dependent variables. All the analysis will be done under the intention to treat principle.

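### 116 per arm gives about 54–64% power for a difference of 0.15, not the stated 90% or more; the number fits a 0.20 difference at 80% power instead

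*Protocol article*

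**What the plan says.** The Sample size section of the protocol article gives a complete set of inputs and a result. On error rates and total it says "Accepting an alpha risk of 0.05 and a beta risk < 0.10 in a bilateral contrast, 232 individuals are needed". The split and the target effect are "116 individuals in the IG and 116 in the CG in order to detect a difference ≥ 0.15 between the two". One group is assumed to have a proportion of 0.5, and on losses it says "A dropout rate of 20% is estimated". The calculation is attributed to the Granmo program, version 7.1.

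The abstract (Method/Design) repeats 232 in total and 116 per group. The Statistical methods section confirms the sidedness: "The level of statistical significance will be set at 0.05, and all tests will be two-tailed".

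**The concern.** Around a proportion of 0.5 the binomial variance is at its largest, so detecting an absolute difference of 0.15 with 90% power takes well over 200 evaluable people per arm. A figure of 116 per arm that is also meant to cope with 20% dropout is less than half of that.

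This is the only justification of the trial's size in the article. It tells readers and the ethics committee that a difference of 0.15 would be missed less than one time in ten. If that is untrue, a null result invites a conclusion of no effect on the strength of power the trial never had.

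**Working it through.** **Inputs, all from the Sample size section** (sidedness also from Statistical methods): alpha 0.05 two-sided, z = 1.960; beta 0.10, z = 1.2816; p1 = 0.50; p2 = 0.65 (0.35 gives the same result by symmetry); 1:1 allocation; 20% dropout.

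**Formula** (pooled-variance comparison of two proportions, per arm), with p̄ the mean of p1 and p2:

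n = [z(α/2)·√(2p̄(1−p̄)) + z(β)·√(p1(1−p1) + p2(1−p2))]² / (p1−p2)²

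**Step 1: try to reproduce 116 from the stated inputs.**
- p̄ = 0.575, so √(2 × 0.575 × 0.425) = √0.48875 = 0.6991
- √(0.25 + 0.2275) = √0.4775 = 0.6910
- n = (1.960 × 0.6991 + 1.2816 × 0.6910)² / 0.15² = (1.3702 + 0.8856)² / 0.0225 = 226.2, so 227 evaluable per arm and 454 in total
- With 20% dropout: 227 / 0.80 = 283.75, so 284 per arm and 568 in total

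The stated 116 is not reproduced, either as an evaluable or as a recruited number.

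**Step 2: see whether another convention explains it.** Pooled, unpooled, arcsine and continuity-corrected formulas, all for a difference of 0.15 from 0.5:

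| Setting | Evaluable per arm | Recruited per arm (÷ 0.80) |
|---|---|---|
| Two-sided, 90% power | 223–240 | 279–300 |
| Two-sided, 80% power | 167–183 | 208–229 |
| One-sided, 80% power | 131–147 | 164–184 |

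None of these two-sample calculations gets down to 116.

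**Step 3: power at the stated size.**

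Power = Φ{[|p1−p2|·√n − z(α/2)·√(2p̄(1−p̄))] / √(p1(1−p1) + p2(1−p2))}

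- n = 116 (nobody lost): (0.15 × 10.770 − 1.3702) / 0.6910 = 0.355, power 63.9%
- n = 93 (116 × 0.80 = 92.8): (0.15 × 9.644 − 1.3702) / 0.6910 = 0.110, power 54.4%

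With a continuity correction these become 58.7% and 48.4%.

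**Step 4: what 116 does correspond to.** For 0.50 versus 0.70 at 80% power (z = 0.8416), p̄ = 0.60:
- n = (1.960 × √0.48 + 0.8416 × √0.46)² / 0.20² = (1.3579 + 0.5708)² / 0.04 = 93.0
- 93.0 / 0.80 = 116.25

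This keeps the protocol's own alpha, baseline proportion and dropout rate, and changes only the difference and the beta.

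**Step 5: detectable difference from 0.5.**

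| Evaluable per arm | 80% power | 90% power |
|---|---|---|
| 93 | 0.20 | 0.23 |
| 116 | 0.18 | 0.21 |

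**The case against.** The arithmetic itself has no good counter. Three arguments bear on its reading and on the remedy.

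**The origin in 0.20 and 80% is inferred.** The article mentions neither figure, and other slips come close. A per-arm number may have been read as a total: 0.425 versus 0.575, two-sided, 90% power and no dropout gives 232 per arm, and so does 0.50 versus 0.65, one-sided, 90% power with 20% dropout (185 / 0.80 = 231.25). A one-sample type of formula, (1.960 + 1.2816)² × 0.25 / 0.15², gives about 116.8 before dropout. This stands as a caution: the document cannot show which slip was made. It does not rescue the sentence, because under every one of these origins 116 per arm falls short of the power claimed.

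**The planned analysis is not a two-proportion test.** The primary outcome is sitting time from activPAL, and Statistical methods names t-tests, repeated-measures ANCOVA and multilevel linear models. The power of those analyses on a continuous outcome could differ from 54–64%. That is fair, and it limits what the figures describe. But the Sample size section gives no mean difference and no standard deviation, so the document contains no other power claim to put in its place.

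**The true target may be larger than 232.** The Recruitment section asks for 30 subjects in each of 13 centres, which is 390. That conflicts with 232 and still falls short: 195 per arm gives 85% power for a difference of 0.15, and 77% with the 156 left after 20% dropout.

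**Conclusion.** The concern holds. On the protocol's own inputs, 116 per arm is about half of the evaluable number required (116 / 227 = 51%) and 41% of the recruited number required (116 / 284). Power for a difference of 0.15 is 54.4% if 116 is the recruited number and 20% drop out, and 63.9% if all 116 are evaluable, against a claim above 90%. The chance of missing such a difference is therefore 46% or 36%.

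These figures assume an individual-level comparison of two proportions with 0.5 in one arm, which is the calculation the section describes. The shortfall does not depend on the choice of standard two-sample formula or on whether 116 already includes dropout. What remains uncertain is only how the number arose. The match with 0.20 and 80% power is exact to rounding, but it is an inference.

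**What to change.** Keep 232 and correct the claim. Remove the beta below 0.10 and the phrase "in order to detect a difference ≥ 0.15 between the two", and replace the power statement with:

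> With 116 participants per arm and 20% dropout (93 evaluable per arm), a two-sided alpha of 0.05 and a proportion of 0.50 in one group, the trial has 80% power to detect 0.50 versus 0.70, and about 54% power for a difference of 0.15.

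This is true of 232 whatever its origin. The sponsor should also record which inputs were entered in the sample size program and reconcile 232 with the 390 implied by the Recruitment section. If 0.15 at 90% power was the real design target, 232 cannot meet it: that would take 568 recruited, and the text should not suggest otherwise.

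The cost is one corrected paragraph and a less favourable power figure. No extra patients are needed, and conduct and analysis do not change.
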